### Power analysis

Since the implementation process is the primary outcome, this study is powered based on the number of individuals with ABI who will receive sports consultancy through the SportMEE programme. Currently, less than 10% of the target population receives sports consultancy via SportMEE. After implementation of the ABI-MOTION intervention, we hypothesise that the reach of the programme will increase to 60%. This means that 60% of participants introduced to the sports consultant during rehabilitation will continue with the optional SportMEE consultancy programme after rehabilitation discharge. Based on these proportions and using an intervention group and a control group with a 3:1 allocation ratio, a two-sided alpha of 0.05 and a power of 0.80, a total sample size of 48 participants is required, 36 in the intervention group and 12 in the control group, as calculated with the Fisher’s exact test. Based on this calculation and taking into account a potential drop-out of 20%, we strive to include a cohort of 60 patients, starting with 15 participants before implementation of the ABI-MOTION intervention, followed by 45 participants in the intervention group after implementation.

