For the explorative effect evaluation, participants are followed up to 1 year after discharge from outpatient rehabilitation and will undergo four measurements; a baseline measurement within the last 4 weeks of outpatient rehabilitation and before the start of the other parts of the ABI-MOTION intervention (T0), and at 3 (T1), 6 (T2) and 12 (T3) months post-rehabilitation discharge. Measurements include physical and cognitive functioning tests at the rehabilitation centre, home measurements including activity monitoring and an electronic diary, and (online) self-report questionnaires sent to the participants by mail or postal mail. The T1 measurement consists of (online) self-report questionnaires only. The T0 measurement aligns with an outpatient rehabilitation visit, and T2 and T3 with standard care follow-up visits at the rehabilitation physician (figure 1). During the visits at the rehabilitation centre (T0, T2 and T3), a trained research assistant conducts the tests, asks general questions and provides information and requirements for the home measurements. To reduce potential burden, participants are given flexibility to complete the questionnaires at their own pace, including the option to pause and resume at a later time. Since implementation outcomes are the primary focus, participants who are unable to complete the questionnaires independently (eg, due to aphasia) are not required to do so. Support of proxies in completing the questionnaires is allowed; however, proxies are asked not to complete the questionnaires on behalf of participants.

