### Statistical and qualitative analyses

Descriptive statistics will be used to summarise the documented numbers related to the evaluation of the implementation process and the outcomes of the effect evaluation. Means and SD will be calculated for variables on an interval scale, and medians and IQRs for ordinal variables and if variables are not normally distributed. Proportions will be calculated for nominal variables. ATLAS.ti software (V.24, ATLAS.ti Scientific Software Development GmbH, Berlin, Germany) will be used to analyse and interpret the qualitative data of the focus groups and network meetings. The dimensions and subthemes of the RE-AIM framework, and the BCW, will be used to thematically identify and describe the themes that are discussed.

The changes over time (T0–T3) of the effect outcomes will be analysed with Generalised Estimating Equations (GEE) models for repeated measurements on an intention-to-treat basis using SPSS (V.32, IBM SPSS Statistics, New York, USA). This method takes all observations into account, even if some outcomes are missing, assuming that these data are missing at random. Each parameter at each time point will be included as the dependent variable in separate GEE models. Independent variables that will be added to each model include measurement time (T0, T1, T2 and T3), group (intervention vs control), and the interaction between time and group. In post-hoc analyses, differences between the intervention and control group at each time point will be analysed. If differences in participant or clinical characteristics between the control and intervention group are present, the models will be adjusted for patient characteristics (eg, age, sex and living status) or clinical characteristics (eg, type of injury, type of treatment and comorbidity). Maximal number of covariates in the model will be based on the number of participants in both groups. Potential differences in participant and clinical characteristics between the control group and intervention group will be calculated using independent t-tests for normally distributed interval scale variables, the Mann-Whitney U test for non-normally distributed interval scale variables, and the χ^2^ test for categorical variables. Interim analyses will be performed when all patients from the control group or intervention group have finished the baseline, 3 and/or 6 months follow-up visits.

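### GEE is planned for all effect outcomes with only about 15 controls; if the uncorrected robust Wald test is used, the joint time-by-group test has about 9 to 11% false positives at a nominal 5%

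*Protocol article*

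**What the plan says.** Under Statistical and qualitative analyses, the article states that the effect outcomes "will be analysed with Generalised Estimating Equations (GEE) models for repeated measurements on an intention-to-treat basis using SPSS". Each outcome has its own model, with the terms "measurement time (T0, T1, T2 and T3), group (intervention vs control), and the interaction between time and group". A second step follows: "In post-hoc analyses, differences between the intervention and control group at each time point will be analysed". The article justifies GEE by its use of all available observations, on the assumption that missing values are missing at random. It does not give the working correlation, the type of standard error, the reference distribution or any small-sample correction.

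Under Power analysis, the cohort is "starting with 15 participants before implementation of the ABI-MOTION intervention, followed by 45 participants in the intervention group after implementation". That comes from a requirement of "36 in the intervention group and 12 in the control group" before allowance for drop-out.

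Under Data collection, "The T1 measurement consists of (online) self-report questionnaires only". Questionnaire outcomes therefore have four visits, and the accelerometer and the physical and cognitive tests have three (Table 4).

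Under Limitations, the effect findings are called exploratory. The small sample is said to restrict covariates and perhaps reduce precision. The level of the tests is not mentioned.

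**The concern.** GEE is a large-sample method. In its usual form it estimates the variance from the participants' own residuals (the sandwich) and compares a Wald statistic with a chi-square distribution. Both steps rely on many independent units. Here the smaller group supplies about 15, and under 3:1 allocation that group contributes most of the variance of every between-group comparison.

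The joint interaction test is the most exposed, because it inverts a covariance matrix of two or three contrasts estimated largely from those few controls. If its true level is near 10% rather than 5%, chance interactions appear about twice as often, over many outcomes. That differs from the loss of precision that the article concedes: imprecision widens an honest interval, whereas an inflated test overstates the evidence.

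**Working it through.** **Inputs.** Group sizes come from Power analysis: 12 and 36 required, 15 and 45 enrolled. The stated figures reproduce. A continuity-corrected two-proportion formula for 10% against 60% at 3:1 gives 12 controls, so 12 + 36 = 48, and exact Fisher power there is 0.900. Drop-out gives 48/0.8 = 60, that is 12/0.8 = 15 and 36/0.8 = 45. The two-sided 5% level is stated only for the reach comparison; it is assumed here for the GEE tests.

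**Number of tested contrasts.** Four visits give an interaction with 3 degrees of freedom, three visits give 2.

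**Bias of the standard error.** With complete data and a saturated time-by-group model, the sandwich variance in a group of size n has expectation (n − 1)/n times the truth. The control group's share of the variance of a between-group difference is (1/12)/(1/12 + 1/36) = 0.75, and the share is the same at 15/45. The ratio of expected to true standard error is therefore about:
- 12/36: √(0.75 × 11/12 + 0.25 × 35/36) = √0.9306 = 0.965, which is 3.5% too small.
- 15/45: √(0.75 × 14/15 + 0.25 × 44/45) = √0.9444 = 0.972, which is 2.8% too small.

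**Level of the joint test.** Simulation with no effect: 20,000 runs per scenario, normal data, the same covariance in both groups, exchangeable correlation 0.5 to 0.8 or AR(1) with 0.7. The statistic is W = d′(CVC′)⁻¹d, where d holds the differences in change, C the contrasts and V the uncorrected sandwich. W is compared with chi-square on 2 or 3 degrees of freedom.

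| Control/intervention | Visits | False positives |
|---|---|---|
| 15/45 | 3 | 8.6–9.1% |
| 15/45 | 4 | 10.3–10.8% |
| 12/36 | 3 | 9.3–9.8% |
| 12/36 | 4 | 12.1–12.8% |

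Monte Carlo error is about √(0.1 × 0.9/20,000) = 0.2 percentage points. Actual GEE fits (1,200 runs, error about 0.9 points) agree:
- 15/45, four visits, 20% drop-out and three covariates: 10.8%.
- 15/45, three visits, 20% drop-out: 10.1%.

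**Where the inflation is smaller or differs.**
- Single contrasts with the same sandwich, normal data: 6.4–7.7%.
- Joint test, lognormal data: 6.1–7.7%. This relief does not extend to the group difference at one time point, which ran at 7.9–8.6% on lognormal data.
- Model-based exchangeable variance, joint test: 3.7–5.2% if the working correlation is right and about 6% if it is wrong. In the latter case a single contrast can reach about 11%.

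**What repairs it (joint test, normal data).**
- Mancl-DeRouen sandwich, still with chi-square: 6.8–9.2%. Correcting the variance alone therefore leaves much of the excess, which shows that the reference distribution is the larger cause.
- The same sandwich with an F reference: 5.8–7.3% with denominator N − 2T (N participants, T visits), and 3.2–4.0% with the number of controls minus 1.
- F test on the pooled covariance: 4.8–5.2%. REML with unstructured covariance and t or F reference: 4.8–5.4%.

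**Scale across outcomes.** Evaluation of intervention effects lists five accelerometer measures, three physical tests and the MoCA (nine with three visits). It also lists two EQ-5D-5L scores, eight SF-36 subdomains and two component scores (twelve with four visits). If all 21 were null and roughly normal, the expected number of significant interactions would be 9 × 0.09 + 12 × 0.105 = 2.1, against 21 × 0.05 = 1.05.

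**The case against.** The strongest reply is that the article states no such test. It names GEE and the model terms. Variance estimator, degrees of freedom and corrections are details that a condensed article may leave to the full protocol or the analysis plan, and nothing in it excludes a correction. This stands, and it makes the inflation conditional. A reader might infer that the planned interaction tests have double the nominal error for every effect outcome, or that the confidence intervals are badly too narrow. The documents support neither. The estimator is unnamed, the shortfall in the standard errors is about 3%, single contrasts are only modestly inflated, and the cost data are to be analysed descriptively.

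Twelve controls is also the pessimistic count. GEE keeps participants with partial data, so the number is nearer 15.

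Finally, the effect evaluation is secondary and exploratory, and the groups are sequential rather than randomised. No confirmatory claim depends on these p-values, and exact calibration would not make the comparison causal. That limits the importance of the point, but a label of exploratory does not make a p-value or interval correct.

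What the reply does not remove is that the article itself chooses GEE for about 15 controls, and justifies it by a missing-at-random assumption that ordinary unweighted GEE does not generally support.

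**Conclusion.** The point holds conditionally. If the robust variance is used with a chi-square reference and no small-sample correction, the joint time-by-group test runs at about 9% (three visits) to 11% (four visits) with 15 and 45 participants. It reaches 12 to 13% only with four visits and 12 controls. Group differences at a single time point run at about 6.5 to 7.5%. The joint-test figures assume roughly normal outcomes and equal covariance in the two groups; on skewed data the joint test is less inflated. With model-based standard errors the joint test is close to nominal if the working correlation is right.

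This is an avoidable weakness in the stated choice of method for an exploratory analysis, not a demonstrated error in a stated test. The reach calculation and the implementation evaluation are untouched.

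**What to change.** For approximately continuous outcomes, replace GEE with a linear mixed model fitted by REML. Keep the same time, group and time-by-group terms, with an unstructured covariance over visits and Kenward-Roger or Satterthwaite degrees of freedom. If correctly specified, this model is also valid under the missing-at-random assumption already stated. Its near-nominal level was shown for normal data with equal covariance in the groups, so residuals and group variances should be inspected.

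Where GEE is kept for non-normal outcomes, state the working correlation and use a bias-corrected sandwich (Mancl-DeRouen or Kauermann-Carroll) together with a t or F reference, naming the denominator degrees of freedom. Alternatively, add a permutation or bootstrap check. The corrected sandwich on its own is not enough, since it still leaves about 7 to 9% for the joint test.

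The cost is a few sentences in the analysis plan, some extra syntax and slightly wider intervals. No new data or participants are needed.

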### Limitations

This protocol has several limitations. First, as this is a hybrid implementation study with a primary focus on implementation outcomes, the pre–post effect evaluation is considered secondary. Consequently, findings should be interpreted as exploratory. In addition, the involvement of researchers in participant recruitment for the effect evaluation limits the ability to fully observe the course of the implementation process and may influence implementation outcomes. Furthermore, the relatively small sample size limits the number of covariates that can be included in the effect evaluation analyses and may reduce the precision of the estimated effect. Finally, as the study is conducted within a specific regional network in the Netherlands, the generalisability of the findings to other settings or healthcare systems may be limited.

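### The missing-at-random statement is attached to unweighted GEE, a method that does not in general support it

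*Protocol article*

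**What the plan says.** Under Statistical and qualitative analyses, changes in the effect outcomes from T0 to T3 "will be analysed with Generalised Estimating Equations (GEE) models for repeated measurements on an intention-to-treat basis using SPSS". The next sentence gives the treatment of missing data: "This method takes all observations into account, even if some outcomes are missing, assuming that these data are missing at random". No weighting or imputation accompanies it.

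The model terms follow: "Independent variables that will be added to each model include measurement time (T0, T1, T2 and T3), group (intervention vs control), and the interaction" of these two factors. Further covariates are conditional: "If differences in participant or clinical characteristics between the control and intervention group are present, the models will be adjusted for patient characteristics" or clinical characteristics. The trigger is thus a difference between groups, not a relation to missingness.

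Two other sections bear on how data may go missing. Data collection says that "participants who are unable to complete the questionnaires independently (eg, due to aphasia) are not required to do so". Power analysis allows for loss without giving a cause: "taking into account a potential drop-out of 20%, we strive to include a cohort of 60 patients". Limitations describes the effect evaluation as secondary and adds: "Consequently, findings should be interpreted as exploratory".

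**The concern.** The sentence credits a method with a property it does not generally have, so this is a wrong statement and not a detail left to a fuller document. Ordinary GEE solves estimating equations on the observed records. These equations have mean zero when data are missing completely at random, or when missingness depends only on covariates in the mean model. If missingness depends on earlier observed scores, which missing at random allows, the equations are generally off centre. How far off depends on the working correlation. Validity under missing at random in general needs a likelihood-based mixed model, weighted GEE, or multiple imputation before GEE.

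The covariate route is not secured here, because a predictor of missingness that happens to be balanced between groups stays out of the model. The questionnaire waiver also links missing self-report data to severity, and these data include the EQ-5D-5L and SF-36, which carry one of the two focus outcomes. If low scorers are lost more often from one group than from the other, the time-by-group term takes up that selection. It can then create or mask an apparent intervention effect, while readers have been told that the method copes.

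**Working it through.** **The plan's own figures.** The sentence at issue carries no number. The nearest figures are the sample sizes, and they reproduce: a continuity-corrected two-proportion calculation (10% v 60%, 3:1, two-sided 0.05, power 0.80) gives 12 + 36 = 48, and 48 / (1 − 0.20) = 60, that is 15 + 45. The point below does not change them.

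**Inputs for the bias.** From the article: GEE with time, group and time-by-group; 20% loss; 15 control and 45 intervention. Assumed, because the article gives no values: within-person correlation ρ = 0.6, outcome SD 1, T0 complete, and 20% missing at follow-up in one group through a logistic model in which lower T0 scores are more often lost (slope 0.5, 1.0 or 1.5 per SD).

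**Formulas, two visits, one group.** Let m be the mean T0 score, in SD, of those still observed at follow-up.
- Independence working correlation: the follow-up mean is the observed-case mean, so bias in mean change = ρ × m.
- Exchangeable working correlation with estimate α: the follow-up mean is corrected by α × m, so bias = (ρ − α) × m. It vanishes when α equals ρ. Selection pulls α slightly below ρ.

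Numerical integration over a normal T0 score gives m and α:

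| Slope per SD | m | α | Independence: 0.6 × m | Exchangeable: (0.6 − α) × m |
|---|---|---|---|---|
| 0.5 | 0.096 | 0.586 | 0.058 | 0.001 |
| 1.0 | 0.173 | 0.557 | 0.104 | 0.007 |
| 1.5 | 0.227 | 0.529 | 0.136 | 0.016 |

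Simulation of the same set-up agrees: about 0.06 to 0.14 SD with independence and 0.002 to 0.017 SD with exchangeable.

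**Four visits.** A large-sample simulation used saturated group-by-time means and about 18 to 19% monotone dropout by T3. Dropout depended on the last observed score (slope 1 per SD), and the within-person correlation was 0.7 exchangeable or 0.8 autoregressive. Bias at T3, in SD:

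| Mechanism | Quantity | Independence | Exchangeable | Unstructured |
|---|---|---|---|---|
| Completely at random | group contrast in change | within 0.004 of 0 | within 0.004 of 0 | within 0.004 of 0 |
| Score-dependent in control only | group contrast in change | −0.12 to −0.13 | 0.00 to 0.01 | about 0 |
| Score-dependent in both groups | group means | 0.11 to 0.13 | within about 0.01 of 0 | within about 0.01 of 0 |
| Score-dependent in both groups | group contrast in change | about −0.006 | below 0.01 | below 0.01 |

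**Scale.** With complete data and ρ = 0.6, the SE of the contrast in change is √[2 × (1 − 0.6) × (1/15 + 1/45)] = √0.0711 = 0.267 SD. The independence bias is therefore 0.058/0.267 = 0.22 to 0.136/0.267 = 0.51 of a standard error. With 20% missing, the simulated SE was 0.30 to 0.32 SD, so the share is somewhat smaller.

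**The case against.** Three stronger readings are tempting, and the article does not support them.

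- **A reader might infer that GEE is valid only under missing completely at random.** That is too absolute. Missingness that depends only on modelled covariates is also covered. For continuous outcomes with a well-chosen working correlation the bias is close to zero, as the tables show. A condensed article may leave the working correlation to a fuller document, so its absence is not a fault in itself.
- **A reader might infer that the plan expects severity-related dropout.** It does not say so. The 20% has no stated cause. The waiver concerns questionnaires, is worded for all participants, and does not cover the accelerometer or the clinic tests.
- **A reader might infer that a mixed model would rescue the waived participants.** The waiver is not limited to follow-up. Someone with aphasia may have no questionnaire at any visit, and a mixed model recovers nothing for that person.

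It is also fair to say that the larger bias needs a different mechanism in each group, which nothing in the article asserts, and that even then it is about half a standard error or less in an analysis labelled exploratory. This limits the consequence but does not make the sentence right. Nor can equal mechanisms be taken for granted: the groups are recruited one after the other and differ in their contact after discharge.

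**Conclusion.** The point stands as a mismatch between method and stated assumption. The article attaches missing at random to unweighted GEE, which supports it only in special cases, and the covariate rule does not secure those cases. Questionnaire non-completion is tied to severity, so the exploratory estimates for self-report outcomes could be biased.

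The size is conditional. With ρ = 0.6 and 20% missing depending on T0 in one group only, the bias in mean change is about 0.06 to 0.14 SD under independence and under 0.02 SD under exchangeable. The contrast bias largely cancels if both groups share the mechanism. Correlation, slopes and group-specific missingness are assumptions, not figures from the article.

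Severity: should-fix. The effect outcomes are secondary, and the primary process evaluation and the sample size are untouched.

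**What to change.** 1. Analyse continuous effect outcomes with a likelihood-based linear mixed model for repeated measures, keeping time, group and time-by-group. SPSS, already the planned software, can fit it.
2. For other outcomes, use multiple imputation before GEE, with earlier scores and severity (including aphasia) in the imputation model.
3. Attach the missing-at-random statement to these methods and remove it from plain GEE.
4. State that participants with no questionnaire data at any visit are not recovered by a mixed model, and report their number by group.

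Cost: revised analysis wording and a little more analysis work, with no new data and no change in sample size. The mixed model relies on a suitable covariance structure. It also covers only missingness explained by observed scores and modelled covariates, so dependence on aphasia beyond the recorded scores would need aphasia in the model or a sensitivity analysis.

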Prior to the implementation of the ABI-MOTION intervention and during the recruitment period of the control group (ie, phase I), the implementation protocol, including the roles of all stakeholders, will be specified and described in more detail. In addition, all study procedures will be discussed with all stakeholders. After finishing inclusion of the control group, the ABI-MOTION intervention will be implemented and inclusion of the intervention group will start. During this second phase, the implementation protocol will be applied and optimised by verifying the implementation determinants described in tables1  2. The corresponding implementation strategies are also verified and may be updated if needed, according to the five steps of the implementation mapping method: (1) analysis of implementation factors, (2) defining change goals, (3) choosing useful theories and congruent strategies, (4) selecting strategies and (5) practical plan for a tailored implementation strategy.^28 30^

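### Confounders enter the effect models only if baseline tests of 15 against 45 people show a difference, which is a poor selection rule for a non-randomised before-after comparison

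*Protocol article*

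**What the plan says.** All of this is in the protocol article; no separate SAP is at hand.

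- **Design.** The Power analysis section plans a cohort of 60, "starting with 15 participants before implementation of the ABI-MOTION intervention, followed by 45 participants in the intervention group after implementation". The section on implementation of the intervention confirms the order: "After finishing inclusion of the control group, the ABI-MOTION intervention will be implemented and inclusion of the intervention group will start". The groups are therefore sequential, not randomised.
- **Base model.** Under Statistical and qualitative analyses, each GEE model contains time (T0 to T3), group and their interaction. Post-hoc analyses then compare the groups at each time point.
- **Adjustment rule.** In the same section: "If differences in participant or clinical characteristics between the control and intervention group are present, the models will be adjusted". The candidates are given as examples only: "patient characteristics (eg, age, sex and living status) or clinical characteristics (eg, type of injury, type of treatment and comorbidity".
- **How a difference is established.** By testing, "using independent t-tests for normally distributed interval scale variables, the Mann-Whitney U test for non-normally distributed interval scale variables", and chi-squared tests for categorical variables. No significance threshold is given.
- **Cap.** "Maximal number of covariates in the model will be based on the number of participants in both groups"; no number follows. The Limitations section adds that "the relatively small sample size limits the number of covariates that can be included in the effect evaluation analyses".

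**The concern.** A variable confounds a group comparison to the extent that it is imbalanced and also predicts the outcome. A baseline significance test measures neither well. It ignores the link to the outcome altogether, and with 15 controls it has little power to detect an imbalance that matters. It can also flag chance differences in variables of no prognostic importance and so use up covariate places that the article itself calls limited.

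In a randomised trial this would be a small matter, because any imbalance would be chance. Here the cohorts come from different periods, and covariate adjustment is the only control of confounding that the analysis section describes. At stake are estimates of physical behaviour and quality of life that keep part of the confounding, and a final model that depends on which tests happened to reach significance. The article states this rule; it is not a detail left open for an analysis plan.

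**Working it through.** **Inputs.** Group sizes 15 and 45 (Power analysis). Tests: t and chi-squared (Statistical and qualitative analyses). Assumed, because the documents do not give them: a two-sided 0.05 threshold, the sizes of imbalance, and a correlation of 0.5 between confounder and outcome.

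**Step 1: the plan's group sizes.** 12 / (1 − 0.20) = 15 and 36 / (1 − 0.20) = 45, total 60. The continuity-corrected formula for 10% vs 60% at 3:1 also gives 12 + 36 = 48. The sample size is not in dispute.

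**Step 2: chance that a continuous imbalance is flagged.** Noncentral t with 15 + 45 − 2 = 58 degrees of freedom and noncentrality d × √(15 × 45 / 60) = d × 3.354.

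| True imbalance d (SD) | Flagged, 15 vs 45 | Flagged, 12 vs 36 |
|---|---|---|
| 0.3 | 17% | 14% |
| 0.5 | 38% | 31% |
| 0.7 | 64% | 54% |
| 0.8 | 75% | 65% |

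The smallest observed difference that reaches significance with 15 vs 45 is t(0.975; 58) × √(1/15 + 1/45) = 2.002 × 0.298 = 0.60 SD.

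**Step 3: a binary factor.** Full enumeration of the uncorrected chi-squared test for 60% vs 40% gives 27%.

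**Step 4: chance flags.** The evaluation section lists about 22 characteristics (10 participant and 12 clinical, counting smoking once). If all were tested with no true imbalance, 22 × 0.05 = 1.1 flags are expected. This expectation does not need the tests to be independent.

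**Step 5: what this does to the estimate.** Simulation of one continuous confounder, one time point, no true effect, 15 vs 45, 6,000 runs per setting. Entries are mean bias in outcome SD.

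| Imbalance | Never adjust | Test, then adjust | Always adjust | Bias removed by the rule |
|---|---|---|---|---|
| 0.3 SD | 0.154 | 0.093 | 0.004 | (0.154 − 0.093) / 0.154 = 40% |
| 0.5 SD | 0.246 | 0.097 | −0.002 | (0.246 − 0.097) / 0.246 = 61% |
| 0.8 SD | 0.398 | 0.052 | −0.001 | (0.398 − 0.052) / 0.398 = 87% |

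Type I error under the rule is 5.4% to 5.8%, against 5.0% to 5.2% with fixed adjustment. At 0.3 to 0.5 SD the root mean squared error is about 0.30 under the rule and 0.26 to 0.27 with fixed adjustment, so the rule also loses on overall accuracy.

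**Step 6: which estimates are affected.** In a linear GEE with complete data, a baseline covariate entered as a main effect shifts the group difference by the same amount at every visit. Fitting such models with and without the covariate, under independence and exchangeable working correlation, leaves the time-by-group estimates and their standard errors unchanged. The group difference at each time point does move. The selection rule therefore matters for the planned post-hoc comparisons, and for variables that influence change over time.

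**The case against.** The strongest reply is that the chance of flagging an imbalance is not the share of confounding removed. A reader might infer from the 17% and 38% that the rule misses most confounding. The figures do not support that: the samples with large observed imbalance are the ones that get adjusted, so the rule removes about 60% of mean bias at 0.5 SD and about 87% at 0.8 SD. The documents give no imbalance sizes, and type I error hardly rises. This part of the reply stands and sets the size of the point.

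It is also fair that the planned model compares change from T0, and that a stable characteristic acting equally at all visits cancels from the interaction when data are complete. That limits the concern but does not remove it, because group differences at each time point are planned as well.

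Two further inferences should be avoided. With 22 independent tests the chance of at least one false flag would be 1 − 0.95^22 = 68%, but the article does not say that all 22 items will be tested, and several are plainly related (length of hospital stay, intensive care, rehabilitation duration). Nor do the documents show that the two cohorts differ in motivation: the Recruitment process section describes one consecutive route for everyone. Such a difference is possible, but not documented.

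Finally, the effect evaluation is declared exploratory, its limited room for covariates is disclosed, and a full covariate list may properly sit in an SAP. None of this repairs a stated rule that makes adjustment depend on baseline tests.

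**Conclusion.** The point holds at moderate severity. Selecting confounders by between-group tests with 15 controls lets imbalances below about 0.6 SD pass more often than not and takes no account of prognostic strength. Under the illustration's assumptions (one confounder, correlation 0.5 with the outcome, 0.05 threshold) it leaves about 0.1 SD of avoidable bias at imbalances of 0.3 to 0.5 SD and about 0.05 SD at 0.8 SD. If many of the listed characteristics are tested, about one chance flag is expected, which may take a scarce covariate place. The consequence is residual bias and a data-dependent model, not a large false-positive rate. It bears mainly on the post-hoc group differences at each time point and on confounders of change. Reach, the outcome on which the study is powered, is not affected.

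**What to change.** Drop the baseline tests as a selection rule. Name a short covariate set in advance by expected prognostic value, for example age, type of injury and pre-injury activity on the Saltin-Grimby scale, all already collected. Include it in every effect model whatever the observed imbalance. Describe baseline imbalance by standardised differences.

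Do not add the T0 outcome as a covariate while T0 is also a dependent observation in the GEE. If baseline-adjusted comparisons are wanted, specify a separate analysis of T1 to T3 with T0 as covariate. That analysis loses people without a T0 value, which can happen because participants who cannot complete questionnaires independently are exempted (Data collection). Where a covariate is expected to influence change, a main effect alone will not protect the time-by-group interaction; say in advance whether its interaction with time is included.

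The cost is a change of wording, made before outcomes are compared between groups, and a few degrees of freedom: 1 + 2 + 1 = 4 if injury is coded in three classes and activity as a score. With 15 controls, or 12 after the planned drop-out, the set must stay small. No covariate set can remove calendar-time effects, and the report should say so.
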